## Abstract

**Background:**

Emotional problems such as anxiety and low mood in children are common, impair everyday functioning and increase the risk of severe mental health disorders in adulthood. Relatively few children with emotional health problems are identified and referred for treatment indicating the need to investigate preventive approaches.

**Methods/Design:**

The study is designed to be a pragmatic cluster randomized controlled trial evaluating the effectiveness of an efficacious school-based cognitive behavior therapy (CBT) prevention program (FRIENDS) on symptoms of anxiety and low mood in children 9 to 10 years of age. The unit of allocation is schools which are assigned to one of three conditions: school-led FRIENDS, health-led FRIENDS or treatment as usual. Assessments will be undertaken at baseline, 6 months and 12 months. The primary outcome measure is change on the Revised Child Anxiety and Depression Scale. Secondary outcome measures assess changes in self-esteem, worries, bullying and life satisfaction. An economic evaluation will be undertaken.

**Discussion:**

As of September 2011, 41 schools have been recruited and randomized. Final 12-month assessments are scheduled to be completed by May 2013.

**Trial Registration:**

ISRCTN23563048

## Background

Emotional problems in children are common with community surveys in the United States and in the United Kingdom indicating that at any one time up to 8% of children aged 5 to 16 years will fulfill DSM diagnostic criteria for a severe anxiety disorder with accompanying significant impairment.
[1,2]. In addition, many more children experience severe anxiety or depressive symptoms that fall below criteria required for a formal diagnosis (that is, sub-threshold) but nonetheless have a significant impact upon everyday functioning. Studies suggest that during childhood and adolescence approximately one in five children will experience incapacitating anxiety or depression
[3-5].

Anxiety and depression significantly impair everyday functioning and increase the risk of mental health disorders in adulthood
[6-9]. The economic burden associated with childhood emotional disorders is not known although it is expected to be considerable
[10]. Although effective psychological treatments are available, few children receive them. The UK National Mental Health Survey found that over an 18-month period only 22% of those children with significant mental health disorders received treatment from specialist child and adolescent mental health services
[11]. In particular, those with emotional disorders were least likely to have contact with specialist services. The limited reach and availability of specialist treatment services alongside a policy shift toward early intervention has led to a growing interest in preventative approaches and a move from clinical to community settings such as schools.

Reviews of school-based emotional health prevention programs for primary school children have found evidence that both universal (provided to all) and targeted/indicated (provided to at-risk children) programs could be effective
[12,13]. Multi-component programs (that is, programs that teach different skills such as relaxation, problem solving, and cognitive awareness) based upon a clear theoretical framework, particularly cognitive behavior therapy (CBT), and which included some parental input (for example, training/information), provide the strongest evidence of effectiveness. The particular benefits of CBT-based programs were also noted in a review of school-based anxiety prevention trials
[14]. Although not formally tested, the effects of CBT programs were marginally larger than non-CBT interventions, with the median effect size for CBT programs of 0.57 indicating a moderate effect. However, there was considerable variation in effect size between studies, suggesting that although the content is important, mediating variables such as adherence to program fidelity, leader rapport, levels of participation and audience appeal are also important factors that will influence effectiveness.

Of the school-based CBT preventive programs that have been developed, the FRIENDS program appears particularly successful
[15]. This was also noted by the World Health Organization, which identified FRIENDS as having strong evidence of being effective as a school-based intervention for anxiety
[16]. The program addresses a number of the issues identified in the reviews highlighted above. It has a clear theoretical model, sufficient sessions, age-appropriate materials, enjoyable and fun activities, a structured leader manual with detailed session plans, standardized leader training, on-going supervision to ensure fidelity, a parent session, and weekly parent contact sheets.

In an initial randomized controlled trial (RCT) involving 489 children aged 10 to 12 years, significant post-intervention reductions in anxiety were reported following FRIENDS
[17]. Trained teachers and psychologists were equally effective in delivering the program
[17]. A subsequent study involving 594 children aged 10 to 13 years found significant reductions in anxiety, which were maintained at 12 months
[18,19]. FRIENDS also had a positive effect upon mood, that is, a reduction in symptoms of low mood, in the high anxiety group. In terms of those with more significant problems, 85% of those in the FRIENDS group who initially scored above the clinical cut-off for anxiety and low mood were diagnosis free at 12 months compared to 31% in the comparison group. The effects appear to last with significant reductions in anxiety being maintained 3 years after FRIENDS
[20]. In addition, comparison between children aged 9 and 10 years and those aged 14 to16 years showed that although both age groups benefited from FRIENDS, the younger group demonstrated the greatest changes in anxiety symptoms
[21]. Although these results are promising, most trials have been undertaken by the program developers in Australia and no RCTs of FRIENDS have been undertaken in the United Kingdom.

## Methods/Design

### Aim of the study

The study has two primary aims:

1. To examine whether a school-based CBT program (FRIENDS delivered by either school or health professionals) is more effective than the usual school curriculum in reducing symptoms of anxiety and low mood in 9- and 10-year-old children (secondary prevention). Total Revised Child Anxiety and Depression Scale (RCADS) scores at baseline and 6 months will be compared for all children. A secondary analysis of the 10% of children in each arm who have the highest total RCADS scores will be undertaken to determine the effect upon the most symptomatic children.

2. To examine the effectiveness of FRIENDS in maintaining good emotional health, that is, to prevent high levels of anxiety and low mood from developing (primary prevention). Total RCADS scores at baseline and 12 months will be compared for the 90% of children who are not the most highly symptomatic.

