### Primary outcome measures

The primary outcome measure notes changes in the level of symptoms on the Revised Child Anxiety and Depression Scale (RCADS)
[23]. This is a recent modification of the Spence Children’s Anxiety Scale
[24], which was revised to correspond more closely to DSM-IV criteria for anxiety and depression
[25]. The 30-item scale (RCADS-30) assesses anxiety in the areas of social phobia, separation anxiety, obsessive compulsive disorder, panic disorder and generalized anxiety disorder and also assesses major depressive disorder. The RCADS-30 has good internal consistency, test-re-test stability and good convergent and divergent validity
[26,27].

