### Statistical analysis

Data analysis will be undertaken blinded to allocation. Analysis and presentation of data will be in accordance with Consolidated Standards of Reporting Trials (CONSORT) guidelines and in particular the extension to cluster randomized trials
[35]. The primary comparative analyses will be conducted on an intention-to-treat (ITT) basis with due emphasis placed on confidence intervals for the between-arm comparisons. Descriptive student- and class-level statistics will be used to ascertain any marked imbalance between the arms at baseline.

The primary analysis will employ a mixed effect linear regression model to compare the active CBT interventions (health- and school-led) versus treatment, adjusting as usual for stratification variables and baseline score, and taking appropriate account of the hierarchical nature of the data (repeated measures, children, classes and schools). Sensitivity analyses making different assumptions will be conducted to investigate the potential effects of missing data.

The extent of missing data will be reported and baseline factors will be compared for completers and non-completers to assess the extent of any bias that may result. Analysis will be undertaken using intention to treat (ITT). The potential for bias, dependent on the extent of missing data, will be assessed. Using the framework specified by White *et al.* an appropriate approach will be used to impute missing values in both outcome and descriptor variables
[36]. A further complete case analysis may also be undertaken and compared to the intention to treat results.

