Secondary analyses will include: 1) repeating the primary analysis adjusting for any variables exhibiting marked imbalance at baseline to examine whether this influences the findings; 2) comparison of children who score high (that is, top 10% of total RCADS scores in each trial arm) and low on anxiety and mood at baseline (that is, remaining 90%) to examine who most benefits from these interventions; 3) similar analyses for other secondary outcomes (using appropriate multi-level models and adjusting *P* values for multiple testing); 4) investigation of process measures such as number of sessions attended; and 5) investigation of possible treatment moderators (for example, gender) and mediators (for example, school pedagogic orientation). Finally, although the study is not sufficiently powered to detect a difference between the two FRIENDS arms (school- and health-led) an exploratory analysis will be undertaken.

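### Two primary aims differ in time point and population, but the single powered comparison and single primary analysis name neither, so the claim protected at 5% is not determined

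*Protocol article*

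**What the plan says.** **Aims.** In the Aim of the study section, "The study has two primary aims". For Aim 1, total RCADS "scores at baseline and 6 months will be compared for all children". The top 10% are examined in an analysis that the same paragraph calls secondary. For Aim 2, "Total RCADS scores at baseline and 12 months will be compared for the 90% of children who are not the most highly symptomatic".

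**Outcome.** Under Primary outcome measures, "The primary outcome measure notes changes in the level of symptoms on the Revised Child Anxiety and Depression Scale (RCADS", with no time point attached.

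**Power.** The Power calculation section covers one comparison, FRIENDS (both delivery modes) against usual PSHE, at 5% two-sided alpha and 80% power. It states no time point and no population.

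**Primary analysis.** In the Statistical analysis section, "The primary analysis will employ a mixed effect linear regression model to compare the active CBT interventions (health- and school-led) versus treatment". The model adjusts for baseline score and is described as "taking appropriate account of the hierarchical nature of the data (repeated measures, children, classes and schools". It names no follow-up time and does not mention the 90%.

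**Secondary analyses.** The list opens with "Secondary analyses will include: 1) repeating the primary analysis adjusting for any variables exhibiting marked imbalance at baseline". Its second item compares the top 10% with those who score "low on anxiety and mood at baseline (that is, remaining 90%) to examine who most benefits from these interventions". Its third item adjusts P values for multiple testing, but only for the other secondary outcomes.

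**The concern.** The aims section makes two results primary, and they differ in both time point and population. The later sections read as though there were one. Nothing says which aim the primary analysis serves, whether it serves both, or how the two aims share the 5%.

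Two things are at stake:

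- **The primary estimand.** With baseline as a covariate, the repeated outcomes in the model are the 6- and 12-month scores. Such a model can yield a 6-month effect, a 12-month effect or some combination, and the article does not say which is primary.
- **The error rate.** If the 6-month result in all children and the 12-month result in the 90% can each be reported as a primary finding at 5%, the chance of at least one false positive is above 5%. If only one is primary, it is not. The article does not settle which case applies.

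**Working it through.** **1. The sections side by side**

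| Section | Contrasts | Time point | Population |
|---|---|---|---|
| Aim of the study, Aim 1 | one, called primary | 6 months | all children |
| Aim of the study, Aim 2 | one, called primary | 12 months | the 90% not most symptomatic |
| Primary outcome measures | RCADS change | not named | not named |
| Power calculation | one, 5% two-sided | not named | not named |
| Statistical analysis, primary | one mixed model | not named (repeated measures) | not named |
| Statistical analysis, secondary item 2 | high versus low scorers | not named | top 10% and remaining 90% |

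No row after the second contains the Aim 2 contrast, which is FRIENDS against usual PSHE at 12 months within the 90%. Secondary item 2 asks whether benefit differs between high and low scorers. That is a treatment-by-subgroup question, not the treatment effect within the 90%.

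**2. The plan's own power figures**

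Inputs from the Power calculation section: ICC 0.02, 28 pupils per class, 90% consent, 80% retention, 45 to 54 schools, SD 12.

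- Consenting pupils: 45 × 28 × 0.9 = 1,134 and 54 × 28 × 0.9 = 1,360.8. Both agree with the article.
- Difference in points: 0.3 × 12 = 3.6. This agrees.
- Detectable effect for the pooled comparison, assuming one class per school and equal thirds of schools: analysed pupils per school m = 28 × 0.9 × 0.8 = 20.16; design effect 1 + (20.16 − 1) × 0.02 = 1.383. MDE = (1.960 + 0.842) × √[1.383 × (1/n₁ + 1/n₂)].
  - 45 schools: n₁ = 15 × 20.16 = 302.4, n₂ = 604.8, MDE = 0.232 SD.
  - 54 schools: n₁ = 362.9, n₂ = 725.8, MDE = 0.212 SD.

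The stated 0.28 to 0.30 SD is therefore not reproduced on these assumptions; it is conservative. That is a separate matter, and the present point does not depend on it.

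**3. Family-wise error if both aims are tested unadjusted at 5%**

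Let Z₁ and Z₂ be the two test statistics under no effect, bivariate normal with correlation r. Then FWER = 1 − P(|Z₁| < 1.96 and |Z₂| < 1.96). For r = 0 this is 1 − 0.95² = 9.75%. The article gives no value for r, so a range is shown.

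| Assumed r | FWER, each test at 5% | FWER, each test at 2.5% |
|---|---|---|
| 0 | 9.75% | 4.9% |
| 0.5 | 9.1% | 4.6% |
| 0.7 | 8.3% | 4.3% |
| 0.8 | 7.8% | 4.0% |
| 0.9 | 7.0% | 3.6% |

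The 90% are a subset of the same children, measured on the same instrument in the same schools, so the higher correlations are plausible.

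**4. What an even alpha split would cost**

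Information needed for equal power: [(2.241 + 0.842) / (1.960 + 0.842)]² = 1.21, about 21% more. At 2.5% the detectable effect at 45 and 54 schools is 0.255 and 0.233 SD in all children. In the 90% (m = 18.14, design effect 1.343) it is 0.265 and 0.242 SD. All four lie below the article's 0.28 to 0.30 SD.

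**The case against.** The strongest reply is that this is a condensed article. Model terms, the named contrast and the handling of multiplicity commonly sit in a statistical analysis plan, which is not shown. The aims do state their own time points and populations. They are also distinct questions, labelled secondary and primary prevention, and whether separate questions need joint alpha control is debated. The analysis section also puts weight on confidence intervals.

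Much of this stands, and it limits the point. Three stronger readings that a reader might infer are not supported:

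- **That the family-wise error exceeds 5%.** This follows only if both aims are tested unadjusted and either success counts as a primary claim. No section states such a rule. If the one primary analysis serves one contrast, there is no inflation.
- **That the secondary list demotes Aim 2.** Item 2 uses the same 90%, but to ask who benefits most. Using that group in a subgroup comparison does not change Aim 2's status. The gap is that Aim 2's own contrast is never restated.
- **That the primary model would dilute a 6-month effect.** As a hypothetical, effects of 0.30 SD at 6 months and 0.10 SD at 12 months would average (0.30 + 0.10)/2 = 0.20 SD under a single common arm effect. But the article does not state a common arm effect and does not exclude an arm-by-time term. The declining effects are invented, and the Background reports earlier reductions maintained at 12 months and at 3 years.

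What the reply does not remove is the mismatch on the face of the article. Two contrasts are called primary, while one comparison is powered and one analysis is called primary, without saying which. An analysis plan can add detail, but the published text would still leave the protected claim open.

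**Conclusion.** The point holds as a mismatch between the aims and the analysis. Two primary aims, at different times and in different populations, are matched by one powered comparison and one primary analysis that identify neither, and Aim 2's contrast is absent from the analysis section. With no order or alpha split, the claim protected at 5% is undetermined.

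The size is conditional: a family-wise error of about 7.0% to 9.75% if both aims are tested at an unadjusted 5%, with the correlation assumed between 0.9 and 0. No size is claimed for dilution of the effect. The conclusion rests on the wording of the sections, not on the power figure.

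**What to change.** Name one primary contrast and use the same label throughout. The aims section supports pooled FRIENDS versus usual PSHE on total RCADS at 6 months in all children, estimated from the mixed model with an arm-by-time term.

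Then give Aim 2 (12 months, within the 90%) one explicit status: either second in a fixed sequence, tested at 5% only if Aim 1 succeeds, or secondary. State its contrast in the Statistical analysis section, separate from the high-versus-low comparison. An even split at 2.5% each would also control the error, at the 21% information cost shown above.

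Align the Aim of the study, Primary outcome measures, Power calculation and Statistical analysis sections, including the list of secondary analyses.

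The cost is wording and one model term, with no extra schools and no loss of power for the first test. The small downside is that Aim 2 cannot be claimed as confirmatory if Aim 1 fails or, if it is labelled secondary, at all.

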### Design

Preventing Anxiety in Children through Education in Schools (PACES) is a pragmatic cluster randomized three-arm controlled trial: FRIENDS delivered by health staff or school staff *versus* usual school curriculum. The arms are summarized in Table 
1.

**Table 1 T1:** Arms of the Preventing Anxiety in Children through Education in Schools (PACES) randomized controlled trial

**Study Arm**	**Content**	**Leader**	**Number of staff**
Treatment as usual	Normal school curriculum	School staff	1
School-led FRIENDS	Structured CBT program	School staff	3
Health-led FRIENDS	Structured CBT program	Health professional	3

Interventions are delivered in schools to whole classes of children as part of the school curriculum. Assessments are undertaken at baseline, 6 and 12 months.

### Participants and eligibility

Interventions are provided as part of the school Personal, Social and Health Educational (PSHE) curriculum. All children in participating classes, that is, year 5 (9 and 10 years old) are eligible to participate. Children are ineligible if they are not attending school (for example, long term sickness, excluded, *etcetera*) or if they do not participate in PSHE for religious or other reasons.

### Ethical approval and consent

The study was approved by the Department for Health Research Ethics Committee at the University of Bath. Consent/assent involves three stages. First, eligible schools were provided with information about the study and interested head teachers were required to provide written confirmation that their school wished to participate. Second, information was posted to the home address of the parents of all eligible children. Parents were invited to return a form opting out of the study if they did not wish their child to complete the study assessments. Finally, children were provided with information about the study and were required to provide signed assent before completing a baseline assessment. Dual carer/child consent/assent was therefore required for assessment completion.

The on-going conduct and progress of the trial is monitored by an independently chaired Data Monitoring and Ethics Committee (DMEC) and a Trial Steering Committee (TSC).

### School recruitment

A list of 268 primary schools in Bath and North East Somerset, and in Swindon and Wiltshire was compiled from Local Authority information. Project information sheets were sent to the head teachers and meetings arranged with the 45 (17%) schools who expressed interest. Four schools did not return signed letters confirming participation before randomization and were therefore excluded. A total of 41 schools were randomized with one school withdrawing after randomization. The cohort therefore consisted of 40 schools (1,448 eligible children).

### Randomization

Allocation of schools took place once all schools had been recruited. Balance between trial arms with respect to key characteristics (school size, number of classes, numbers of children in year 5 classes, preferred term of delivery, preferred day of delivery, mixed-year 5 classes (that is, classes that were year 4 and year 5 combined and classes that were year 5 and year 6 combined) or single year 5 classes and level of educational attainment) was achieved by calculating an imbalance statistic for a large random sample of possible allocation sequences
[22]. A statistician with no other involvement in the study randomly selected one sequence from a subset with the most desirable balance properties.

### Intervention

FRIENDS is a manualized cognitive behavior therapy (CBT) program designed to improve children's emotional health. Each child has their own workbook and group leaders have a comprehensive manual specifying key learning points, objectives, and activities for each session. The intervention trialed in this study involves nine, 60-minute weekly sessions delivered to whole classes of children. Through a range of age-appropriate fun activities including stories, quizzes, role plays and games, children learn practical skills to control their anxiety. They are helped to identify their feelings and to learn to relax, thereby managing their anxious feelings. They are helped to identify unhelpful thoughts (anxiety increasing) and to replace them with more helpful (anxiety reducing) thoughts. Finally, they are helped to face and overcome their problems and challenges rather than avoid them. Written work is kept to a minimum and each session uses a variety of different materials and activities to engage and maintain the interest of the children. Initial training and regular supervision of class leaders will be provided by an accredited FRIENDS trainer.

An additional session for parents/carers is conducted to provide parents with an overview of the program, the CBT rationale, and the skills the children will learn. In addition, parents receive a summary sheet detailing the key learning points of each session and the ideas their child will be practicing so that they can reinforce and encourage their use at home.

